## Abbreviations

|     |                           |
|-----|---------------------------|
| CI  | Confidence Interval       |
| DBP | Diastolic Blood Pressure  |
| IQR | Interquartile Range       |
| NMB | Neuromuscular Blockade    |
| RCT | Randomized Clinical Trial |
| SAP | Statistical Analysis Plan |
| SBP | Systolic Blood Pressure   |
| SD  | Standard Deviation        |
| TOF | Train of Four             |

## 1. Introduction

The aim of this project is to evaluate in a single-center randomized clinical trial (RCT) whether the use of additional lidocaine could influence the NMB enhancement. Thus, this study's primary endpoint is the time at which spontaneous recovery of a train-of-four (TOF) ratio of 90% will be achieved (complete duration). The secondary endpoints are other NMB characteristics (onset time, duration 25, duration 95) and hemodynamic parameters.

This statistical analysis plan (SAP) will give more detailed descriptions of the endpoints in the study and the corresponding analyses.

## 2. Study design

Sixty-four patients [American Society of Anesthesiologists (ASA) physical status I to II, aged 18 to 60 years] who will be scheduled for surgery (estimated surgical time greater than 90 min, with similar pain stimulus and no need for a continuous neuromuscular block during the surgical procedure) will be recruited. The exclusion criteria are patients with diseases or on medications known to interfere with neuromuscular transmission, hepatic or renal dysfunction, electrolyte abnormalities that can potentiate blockade, an allergy to the drugs used in the study, a body mass index  $<18$  or  $>29$  kg.m^-2, and those who are expected to have difficulties during mask ventilation or intubation, pregnant or breastfeeding.

The patients will be randomly and equally allocated into four groups (figure 1). The Computer-generated randomization will be stratified by gender to pursue equal distribution of intervention and control group for both male and female subjects, and the allocation concealed with sequentially numbered, sealed, opaque envelopes. The envelope's seal will be broken before the induction of general anesthesia by trained study personnel not involved in the data collection. Throughout the perioperative period, care providers, patients, and research team members will be blinded to the group assignments.

*Figure 1 Flowchart of screening and inclusion process*

[figure not shown]

## 2.1 Sample size calculation

The primary outcome measure for the power calculation is the elapsed time for the TOF (T4/T1) recovery response to 90% of the original value after infusion of cisatracurium. For the sample size calculation, we considered a previous study showing magnesium sulfate prolonged the complete duration of rocuronium-induced NMB (*Acta Anaesthesiol Scand* 2010, 54(3):299-306). Having chosen a significance level of 5% and a power of 80%, we applied Satterthwaite's approximation (*Stat Med* 2001, 20(7):1089-1095). The result revealed N=14 patients per group, and we decided to randomized 16 patients in each group to allow for drop-outs.

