## 6. Analyses

All outcomes will be presented using descriptive statistics, normally distributed data by the mean and standard deviation (SD), and skewed distributions by the median and interquartile range (IQR). The Shapiro-Wilk test will be used to assess normality. The pharmacodynamic variables, clinical and demographic characteristics will be compared between the groups via the Kruskal-Wallis test, followed by Dunn's multiple comparison test or one-way ANOVA followed by the Tukey multiple comparison test, or the chi-square test, where appropriate. The area under the curve (AUC) will compare the study groups' hemodynamic responses. A p-value <0.05 will be considered statistically significant for all outcome variables. GraphPrisma version 8.3 will be used for all statistical analyses.

The subsections below will describe analyses in addition to the descriptive statistics.

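### The sample size in SAP section 2.1 makes no visible allowance for the four-group comparisons in section 6, where power per pair would be about 60% (Tukey) or 48% (Dunn), and section 6.1 does not settle which comparison is primary

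*SAP*

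**What the plan says.** Section 2.1 sizes the trial on the time to a TOF ratio of 90%: "Having chosen a significance level of 5% and a power of 80%, we applied" Satterthwaite's approximation. The effect comes from "a previous study showing magnesium sulfate prolonged the complete duration of rocuronium-induced NMB". The result is 14 per group, with 16 randomized to allow for drop-outs. The section states no assumed difference, SD, sidedness, pair of groups or multiplicity adjustment.

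Section 2 allocates patients equally to four groups. Section 6 compares the pharmacodynamic variables by Kruskal-Wallis followed by Dunn, or by "one-way ANOVA followed by the Tukey multiple comparison test", at p<0.05. The primary outcome belongs to these variables, since section 4.2 lists the secondary ones as the other pharmacodynamic measures.

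Section 6.1 describes the primary analysis differently: a model with treatment groups as fixed effects, giving an estimated difference and 95% CI. It mentions neither Tukey nor Dunn, and no pair.

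The question in section 1 is "whether the use of additional lidocaine could influence the NMB enhancement". Section 3 places this on a cisatracurium block, with lidocaine given together with magnesium sulfate.

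**The concern.** Satterthwaite's approximation adjusts the degrees of freedom of a two-sample comparison with unequal variances, and only one drug effect is cited. The natural reading is that the 80% belongs to one pair of groups at an unadjusted 5%. Tukey or Dunn over four groups controls the error across six pairs by raising the critical value, so 14 per group cannot also give 80% for each pair.

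The assumed effect is also not the one under study. It is magnesium's effect on a rocuronium block, and nothing in section 2.1 says why lidocaine's increment on a cisatracurium block should be as large.

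If this stays as it is, a non-significant lidocaine comparison could be reported against a stated power of 80% that was not calculated for that test or that effect.

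**Working it through.** **Inputs from the SAP.** Significance level 5%, power 80%, 14 computed and 16 randomized per group (section 2.1); four equal groups (section 2), hence 4×3/2 = 6 pairs; Tukey or Dunn (section 6).

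**Assumptions.** Two-sided test, one unadjusted pair behind the 80%, equal variances, normal data.

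**1. The plan's own figure.** N=14 cannot be reproduced, because no difference or SD is given. It can be inverted for the standardized difference d.
- Normal approximation: d = (1.960 + 0.842) × √(2/14) = 1.06.
- Noncentral t, df 26, critical t 2.056: 80% power at d = 1.10.
- Upper end: d = 1.145 if N was rounded up from just over 13; about the same with the lowest Satterthwaite df of 13.

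The working value is d = 1.10.

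**2. Tukey.** Critical t = q(0.95; 4, df)/√2, noncentrality = d√(n/2), df = 4n − 4.

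| n per group | df | q | critical t | noncentrality at d=1.10 | power at 1.10 | power at 1.145 |
|---|---|---|---|---|---|---|
| 14 | 52 | 3.753 | 2.654 | 2.910 | 60.3% | 64.7% |
| 16 | 60 | 3.737 | 2.643 | 3.111 | 68.0% | 72.3% |

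At d = 1.06 the Tukey power with 14 per group is 56%. The difference detectable with 80% power is 1.33 SD at 14 and 1.24 SD at 16. Holding 80% at 1.10 SD would take about 20 evaluable per group.

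**3. Dunn.** Pooled ranks, z = difference in mean ranks / √[N(N+1)/12 × 2/n] with N = 4n, Bonferroni over six pairs (critical z 2.638), 20,000 simulated trials with normal data.
- One group shifted by 1.10 SD: 48% at 14, 56% at 16.
- Means 0, 0, d, 2d, for the pair that differs by d: 32% at 14, 42% at 16.

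A t test with the same Bonferroni correction gives 56.9% at 14 and 64.9% at 16. That is not Dunn's power, because Dunn works on pooled ranks.

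**4. The section 6.1 model, no adjustment.** One contrast with the variance pooled over four groups (df 52, critical t 2.007): 81.5% at 14 and 86.5% at 16, at d = 1.10. If all six pairs are tested at 0.05 and all means are equal, the familywise error is P(range statistic > 2.007 × √2), which is about 20%. Six independent tests would give 1 − 0.95⁶ = 26.5%; pairs that share groups are correlated, so 20% is the relevant figure.

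**The case against.** The strongest reply is section 6.1. It is the section for the primary outcome, and it uses neither Tukey nor Dunn. If it governs and one contrast is tested, the 80% is met. This stands: the loss of power is conditional on section 6 governing. It does not settle the matter, because section 6 also covers the primary outcome and section 6.1 names no pair. With all six pairs unadjusted, the power is kept at the price of error control.

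Second, the single-pair, two-sided basis is inferred, and the figures move with it. A one-sided 5% would imply d = 0.97 and Tukey power of 47%. Sizing at 5%/6 would give about 85%. Sizing on a four-group F test would give roughly 56% to 78%, depending on the pattern of means. This also stands, although section 2.1 indicates none of these alternatives.

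Third, section 2.1 openly says where the effect came from, and borrowing from a related drug is a judgement, not a mistake. Agreed. What is absent is the assumed difference and SD, and the size of lidocaine effect that the trial could detect.

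A reader might infer that N=14 is an arithmetic error, or that the trial simply lacks 80% power. The SAP supports neither: N=14 can be neither reproduced nor refuted, and a single unadjusted contrast reaches about 80%. Nor does one figure of 60% cover both tests, since it applies to Tukey only.

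**Conclusion.** The concern holds in conditional form. Section 2.1 shows no allowance for multiple comparisons. If section 6 governs, power per pair at the implied 1.10 SD is about 60% (Tukey) or 48% (Dunn, one group shifted) with 14 per group, and about 68% or 56% with all 16 evaluable. If section 6.1 governs, power per pair is kept, but testing all six pairs carries a familywise error of about 20%. Only one contrast named in advance keeps both 80% power and 5% error, and the SAP names none. Under every reading, the 80% was not derived for lidocaine's added effect on a cisatracurium block. The figures rest on the four assumptions listed in the working; the need to name the comparison does not.

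**What to change.** 1. Reconcile sections 6 and 6.1, so that one analysis of the primary outcome remains.
2. Name one primary contrast for the stated question, tested at two-sided 5%. Lidocaine plus magnesium versus magnesium would fit, if these are among the arms in figure 1, which the available text does not show. With 14 per group this has about 80% power at 1.10 SD. Make the other pairs secondary, with adjustment.
3. If all pairs are to stay primary, restate the power in section 2.1 for the test used, Tukey and Dunn separately, with detectable differences of 1.33 SD (14 per group) or 1.24 SD (16 per group) under Tukey.
4. In either case, add to section 2.1 the assumed difference, SD, sidedness and pair of groups, and state in minutes the smallest lidocaine effect that the trial can detect with 80% power.

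The cost is SAP wording, to be settled before unblinding, and no more patients. The price is either that the other pairs lose primary status or that the stated power becomes less favourable.

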## 3. Aims and objectives

To investigate the effects of lidocaine associated with magnesium sulfate on the neuromuscular blockade promoted by cisatracurium and evaluate its possible hemodynamic repercussions.

## 4. Outcomes

This section will present the outcomes investigated to answer the study aims and objectives. The analyses are described in section 6- Analyses.

### 4.1 Primary outcome

Complete duration (T4/T1=90%): elapsed time for the TOF (T4/T1) recovery response to 90% of the original value after infusion of cisatracurium. This outcome measure will be presented in minutes.

### 4.2 Secondary outcomes

Other pharmacodynamic measures:

1. Latency (Onset time 5): elapsed time to reduce the response of T1 to 5% of the initial contraction force after the infusion of cisatracurium.
2. Clinical Duration (DURATION 25%): the elapsed time for T1 recovery = 25% (Dur25%) of the original value of T1 after the infusion of cisatracurium.
3. Recovery Index (DURATION 25%-75%): the elapsed time between the T recovery=25% and 75% (Dur75%) after cisatracurium infusion.
4. Total Duration (Duration 95%): the elapsed time for T1 recovery of the response to reach 95% of the initial value after cisatracurium infusion.

## Hemodynamics

### 1. Mean Arterial Pressure (MAP) and Heart Rate (HR) during the Induction Period

These measures will be obtained at the following time points: (1) when the patient arrived in the operating room, (2) immediately before induction, (3) immediately before infusion of the solutions, (4) immediately after infusion of the drugs, (5) immediately before tracheal intubation, and (6) one minute after the tracheal intubation.

### 2. Mean Arterial Pressure (MAP) and Heart Rate (HR) during the Maintenance Period

These measures will be obtained every 15 min until complete neuromuscular recovery.

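### The maintenance-period AUC for MAP and HR has no common time window, so as written it lengthens with the block and can confuse a duration effect with a hemodynamic one

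*SAP*

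**What the plan says.** Four parts of the SAP bear on this.

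- **Section 4.2, Hemodynamics, Maintenance Period** sets the reading schedule: "These measures will be obtained every 15 min until complete neuromuscular recovery". Each patient therefore has an individual end time.
- **Section 4.1** defines the primary outcome: "Complete duration (T4/T1=90%): elapsed time for the TOF (T4/T1) recovery response to 90% of the original value after infusion of cisatracurium".
- **Section 6** names the summary used to compare groups: "The area under the curve (AUC) will compare the study groups' hemodynamic responses". It does not say over which interval, whether the area is divided by time, or whether a baseline is subtracted.
- **Section 6.2** describes hemodynamic analysis a second time. It refers to the primary-outcome method with the variable's own baseline value as covariate, and mentions neither the AUC nor unequal observation lengths.

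Section 2.1 shows that prolongation is the effect the trial is planned around: "we considered a previous study showing magnesium sulfate prolonged the complete duration of rocuronium-induced NMB".

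**The concern.** An AUC is level multiplied by time. MAP and HR are always positive, so an unnormalised AUC must increase with the length of observation. Here that length ends at complete recovery, which is in effect the event that defines the primary outcome. If treatment prolongs the block, the treated groups collect more area even when their pressures and heart rates match those of the other groups.

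The error can run either way. A pure duration effect may be reported as a hemodynamic effect. A real fall in pressure in the group with the longest block may be offset by the extra minutes and go unseen. Section 3 makes hemodynamic repercussions part of the trial's objective, so the summary should measure level rather than duration.

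**Working it through.** **1. The plan's own figure.** The SAP gives no figure for the AUC analysis. Its only computed figure is the sample size: "The result revealed N=14 patients per group, and we decided to randomized 16 patients in each group to allow for drop-outs". The difference and SD behind it are not stated, so 14 cannot be reproduced forwards. Solved backwards for one pairwise comparison (two-sided 5%, 80% power):

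- Normal approximation: d = (1.960 + 0.842) × √(2/14) = 1.06.
- Two-sample t-test: d = 1.10.
- Allowance: 14/(1 − 0.125) = 16, and 4 × 16 = 64, both consistent with the SAP.

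The plan's own N therefore implies a prolongation of about 1.1 SD. I use that as the duration effect below.

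**2. Direct arithmetic (assumed MAP 80 mmHg; assumed durations 75 and 90 min).**

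- 80 × 75 = 6000 mmHg·min.
- 80 × 90 = 7200 mmHg·min, which is 7200/6000 = 1.20, or 20% more with no pressure difference.
- 6000/90 = 66.7 mmHg. A patient 13.3 mmHg lower for 90 min has the same AUC as one at 80 mmHg for 75 min. This is a chosen exact cancellation, shown only to illustrate the mechanism.

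**3. Four-group simulation.** From the SAP: four groups of 16, a 15-min grid stopping at each patient's recovery, ANOVA or Kruskal-Wallis at 0.05. Assumed: mean recovery 75 min in unprolonged groups; SD 10, 15 or 20 min; prolongation 1.1 SD (11, 16.5 or 22 min) in one or two groups; MAP mean 80, between-patient SD 10, within-patient SD 6, flat over time. There were 1000 runs per scenario, so the Monte Carlo standard error at 5% is √(0.05 × 0.95/1000) = 0.7 percentage points.

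| Summary measure | Rejections, MAP identical, duration prolonged | Rejections, true 12 mmHg fall in the one prolonged group |
|---|---|---|
| Raw AUC, ANOVA | 55% to 86% | 6% to 17% |
| Raw AUC, Kruskal-Wallis | 52% to 84% | 5% to 16% |
| AUC minus an assumed common baseline of 95 mmHg, ANOVA | 8% to 19% | 98% to 100% |
| AUC divided by observed time, ANOVA | 4% to 6% | 92% |
| Mean over 0 to 45 min, ANOVA | 4% to 6% | 92% |

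With no prolongation in any group, raw AUC rejected in 5% to 6%, so the inflation comes from duration alone.

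In the masking scenario with SD 15, the group with the lower pressure had the larger mean AUC: 5715 against about 5411 mmHg·min. The baseline-subtracted AUC does not mask the fall, because the deficit also accumulates with time. For the same reason it mixes duration into the estimated effect.

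**4. Dependence on the duration effect.** A two-group simulation (assumed MAP 80 ± 8, duration 75 ± 15 min, n = 16 per group, 20,000 runs) gave raw-AUC rejections of 5.2%, 22.8%, 66.3% and 74.6% at duration shifts of 0, 0.5, 1.0 and 1.1 SD. The time-weighted mean stayed at about 5% throughout.

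**The case against.** **The SAP never says that the AUC runs to recovery.** This is correct. Section 4.2 is a measurement schedule and section 6 is one sentence without a window. A reader might infer that the plan expressly defines an AUC accumulated to recovery; it does not. The point rests on reading the two sections together, where no other interval or normalisation is offered. What can be said is that the plan as written leads to, or at least permits, the distorted summary.

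**Raw AUC may not be the governing analysis.** Section 6.2 plans a baseline-adjusted analysis without naming AUC, and a baseline-subtracted AUC is not excluded. This has weight. It means that sections 6 and 6.2 need reconciling, and it lowers the plausible distortion to 8% to 19% under the subtracted form. It does not remove the problem, because a baseline covariate does not correct for unequal observation time.

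**The sizes are assumed.** This also stands. MAP level, spread, mean duration and its SD are not in the SAP. The direction for raw AUC needs none of them.

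**The induction-period AUC.** A reader might extend the criticism to it, since three of the six readings precede the study solutions. The documents do not support that. The six events are common to all patients, so there is no duration bias. Any dilution depends on spacing that the SAP does not give and on which baseline section 6.2 means. Under an assumed equal spacing, post-drug shift of 0.8 SD and correlation of 0.6, power of the six-point AUC moved from 26% unadjusted to 65% or 99%, depending on the baseline covariate.

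**Dividing by time is not a complete cure.** This is accepted. If MAP drifts, longer blocks average over later readings. With an assumed common drift and no treatment effect, the time-weighted mean rejected in about 8% to 12%, with the 9% to 12% figures arising at 0.2 to 0.3 mmHg per minute. A fixed window stayed near 5%.

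**Conclusion.** The concern holds for the maintenance period. As written, the AUC comparison of MAP and HR lengthens with the primary outcome, so it can show a difference that is only duration and can hide a real fall in the longer-block group. Under the stated assumptions, with a 1.1 SD prolongation taken from the SAP's own N, false positives are 55% to 86% for raw AUC and 8% to 19% if baseline-subtracted, against about 5% once the window is common or the area is normalised. Raw AUC found a true 12 mmHg fall in only 6% to 17% of trials, against about 92%. These rates would change with other inputs, and they vanish if treatment does not change duration.

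The finding is limited to a secondary outcome. The primary outcome, sample size and data collection are untouched. It should be fixed before the data are analysed, but it does not threaten the main result.

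**What to change.** Amend section 6 along these lines:

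- **Main analysis:** compute the maintenance AUC, or the mean, of MAP and HR over a fixed window common to all patients. Name its length before the data are seen, keep it short enough that patients are still under observation throughout, and state how anyone who recovers earlier is handled.
- **Supporting analysis:** AUC divided by each patient's own observation time, which uses every reading, with a note that it can be mildly biased if MAP or HR drifts.
- **Covariate:** the reading immediately before infusion of the solutions.
- **Consistency:** state that this is the hemodynamic analysis meant in section 6.2, so that the two sections describe one method.

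The cost is SAP wording only, because the same data are used. The downside is that the fixed window leaves late readings out of the main comparison; the supporting analysis brings them back. The 0 to 45 min window used in the check was an illustration, not a recommendation.

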## 4.3 Safety outcomes

### Adverse events

Any adverse events will be documented.

## 5. Populations and subgroups to be analyzed

### 5.1 Populations

All randomized study subjects. This will be seen as the primary population for the analysis.

### 5.2 Subgroups

Not applicable

## 6. Analyses

All outcomes will be presented using descriptive statistics, normally distributed data by the mean and standard deviation (SD), and skewed distributions by the median and interquartile range (IQR). The Shapiro-Wilk test will be used to assess normality. The pharmacodynamic variables, clinical and demographic characteristics will be compared between the groups via the Kruskal-Wallis test, followed by Dunn's multiple comparison test or one-way ANOVA followed by the Tukey multiple comparison test, or the chi-square test, where appropriate. The area under the curve (AUC) will compare the study groups' hemodynamic responses. A p-value <0.05 will be considered statistically significant for all outcome variables. GraphPrisma version 8.3 will be used for all statistical analyses.

The subsections below will describe analyses in addition to the descriptive statistics.

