### 6.1 Primary outcome

The primary analysis will compare intervention groups on their mean change in NMB. The difference in time course to TOF=90% will be the dependent variable. Study subjects will be considered as random effects and treatment groups as fixed effects. The estimated difference in mean change from baseline and the corresponding 95 % confidence interval (CI) will be presented.

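### Baseline characteristics are tested between randomised groups, which is uninformative, while the primary model leaves out gender, age and BMI, at some cost in precision

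*SAP*

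**What the plan says.** SAP section 6 puts baseline variables through the same tests as the outcomes: "clinical and demographic characteristics will be compared between the groups" by Kruskal-Wallis with Dunn's test, or by one-way ANOVA with Tukey, or by chi-square. It attaches no action to the results. The stated threshold, "A p-value <0.05 will be considered statistically significant for all outcome variables", refers to outcomes, so no threshold is fixed for baseline variables.

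Section 6.1 describes the primary model: "Study subjects will be considered as random effects and treatment groups as fixed effects". It names no covariate. Section 6.2 names one, the outcome's own baseline value, for the secondary outcomes.

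Section 2 stratifies the randomisation by gender. It restricts entry to patients "aged 18 to 60 years" with BMI between 18 and 29 and ASA status I or II, so age and BMI must be known for every patient before randomisation.

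**The concern.** There are two linked weaknesses.

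- **The tests answer no useful question.** Allocation is random, so any baseline difference is due to chance. A small p-value reports a chance event, and a large one does not show that the groups are alike. What matters is how large the imbalance is and how strongly the variable predicts complete duration. The p-value gives neither.
- **The analysis does nothing with baseline information.** The design treats gender as important enough to stratify on, yet the primary model omits it. Age and BMI are on file and also unused. If any of these predicts complete duration, the confidence interval is wider than it needs to be, and a chance imbalance in the realised trial passes into the estimated difference.

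**Working it through.** **Inputs from the SAP.** Four equal groups and 64 patients (section 2). Section 2.1: "Having chosen a significance level of 5% and a power of 80"%; "The result revealed N=14 patients per group"; "we decided to randomized 16 patients in each group to allow for drop-outs".

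**Assumptions.** Two-sided 5% tests; six independent baseline variables; correlation r of a covariate with duration of 0.3 to 0.5; joint R-squared of age and BMI from 0 to 30%. The SAP gives none of these.

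**1. The plan's own figure.** N=14 cannot be reproduced, because no difference or SD is stated. Back-solving a two-group t-test (26 df, noncentrality d × √(14/2)) for 80% power gives d = 1.10 SD. The normal approximation gives 1.06. The 1.10 SD is used below as a yardstick only.

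**2. Power of a baseline ANOVA, 16 per group.** Noncentrality is 16 × the sum of squared deviations of the group means, on 3 and 60 df, with critical F 2.76.
- One group shifted by 0.5 SD: noncentrality 3.0, power 26%.
- Two groups at ±0.25 SD and two at 0: noncentrality 2.0, power 18%.
- For a 1.0 SD imbalance the two patterns give 81% and 62%.

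**3. How often chance imbalance arises.**
- One given pair: SE of the gap = √(2/16) = 0.354 SD, so P(|gap| > 0.5 SD) = 16%.
- Largest of the six pairwise gaps (simulation): above 0.5 SD in about 49% of trials, with the ANOVA non-significant in about 90% of those. For 0.7 SD the figures are about 19% and 75%.
- At least one p<0.05 among six tests: 1 − 0.95^6 = 26.5%.

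**4. What an imbalance does to an unadjusted comparison.** Shift = r × gap. For a 0.5 SD gap this is 0.15 to 0.25 SD at r = 0.3 to 0.5, or 14% to 23% of 1.10 SD. At r = 0.5 the shift is 0.25/0.354 = 0.707 SE and the residual SD factor is √(1 − 0.25) = 0.866. The conditional two-sided error is then 1 − Φ((1.96 − 0.707)/0.866) + Φ((−1.96 − 0.707)/0.866) = 7.5%. For a 0.7 SD gap it is 13%.

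**5. Gain or loss from adjusting for age and BMI.** With two chance-imbalanced covariates, SE ratio ≈ √[(1 − R²)(1 + 2/(64 − 4 − 2 − 1))] = √[(1 − R²) × 1.0351]. Power is for one pairwise Tukey comparison at 1.10 SD with 16 per group. Unadjusted, the noncentrality is 1.10/0.354 = 3.11 against a critical value of 2.64, giving 68%.

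| R² | SE ratio | Power |
|---|---|---|
| 0 | 1.017 | 66% |
| 10% | 0.965 | 72% |
| 20% | 0.910 | 78% |
| 30% | 0.851 | 84% |

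The SE breaks even at R² = 1 − 1/1.0351 = 3.4%. Power breaks even at about 3.6%, because two degrees of freedom are also spent. Simulation of the same model agrees to within about half a point of power.

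**6. Adding gender.** Stratification keeps gender close to balanced, so its cost is mainly one more degree of freedom. In the same calculation, going from 58 to 57 df lowers power by about 0.1 point.

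**The case against.** The strongest reply is that nothing here is an error in the primary analysis. That stands. An unadjusted comparison of randomised groups is valid on average, and its standard error already allows for chance imbalance. A reader might infer from the 7.5% and 13% figures that the trial's type I error is inflated. It is not: those figures are conditional on a particular imbalance, and over all randomisations the rate is nominal.

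Other parts of the reply also stand:

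- A reader might infer that the baseline p-values would decide the covariates or alter the primary result. The SAP attaches no consequence to them, so deleting them changes no estimate.
- A reader might infer that the tests can detect no imbalance. They have low power at 0.5 SD, but 62% to 81% at 1 SD.
- Baseline variables are not wholly unused. Gender enters the randomisation, and eligibility restricts age, BMI and ASA status, which could weaken their correlation with duration.
- The 49% concerns the worst of six pairs; for a given pair it is 16%. A shift of 0.15 to 0.25 SD is less than one SE (0.354 SD).
- The SAP does not say that age or BMI predicts duration, so the benefit is assumed.

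Section 6.2 might be read as carrying a covariate back into 6.1. That would be the outcome's own baseline, not a demographic variable, and a time from infusion to TOF 90% has no pre-treatment value.

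The reply does not rescue the tests, which remain uninformative under any assumption, and it does not explain why the stratification factor is absent from the model.

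**Conclusion.** The point holds as one of efficiency and good practice, not of validity. That the baseline tests are uninformative follows from the randomisation alone and needs no numerical assumption. The case for including gender rests on the SAP's own design. The case for age and BMI is conditional. Power rises by about 4 to 16 points if they jointly explain 10% to 30% of the variance in complete duration, is unchanged near 3% to 4%, and falls by about 2 points, with a standard error about 1.7% larger, if they explain nothing. These figures assume a normal linear model, 16 analysed per group, Tukey comparisons and the back-solved 1.10 SD, which the SAP does not state. Severity is minor to moderate.

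**What to change.** - **Section 6:** remove clinical and demographic characteristics from the list of variables to be tested, and present them by group with descriptive statistics and no p-values.
- **Section 6.1:** prespecify gender, age and BMI as fixed covariates in the linear model for complete duration, kept whatever imbalance is observed, and report the unadjusted estimate with its confidence interval beside the adjusted one.
- **Link between the two:** state that this linear model is the primary analysis. The Kruskal-Wallis route that section 6 also offers for the pharmacodynamic variables has no place for covariates.

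No new data are needed, as all three variables are already recorded for stratification or eligibility. The cost is a change of SAP wording, three model degrees of freedom, and the small loss of power given above if age and BMI turn out not to be prognostic. The change should be made before unblinded data are seen.
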